## Abstract

**Background:** Acute bronchitis (AB) is a common disease in pediatrics. Prolonged AB may develop into chronic bronchitis. Bronchitis caused by the influenza virus can lead to severe hypoxia or insufficient ventilation, causing great harm to patients and increasing the burden on children and society. Presently, there is no specific treatment for AB except symptomatic supportive treatment. It is urgent to find an effective treatment for AB. Jinzhen Oral Liquid (JZOL) has been found to have a broad spectrum of anti-inflammatory and antiviral effects in previous clinical and basic studies and has a good effect on AB in children. However, the large-sample, randomized, double-blind, head-to-head, evidence-based studies are lacking. The purpose of this protocol is to evaluate the efficacy, safety, and mechanism of JZOL in the treatment of AB in children.

**Methods:** This is a randomized, double-blind, parallel-controlled multi-center clinical trial. The sample size is 500 participants in the intervention group and the control group respectively, with a total of 1000 participants. They will be recruited by 10 hospitals in China. The Intervention group takes JZOL and Ambroxol Hydrochloride and Clenbuterol Hydrochloride Oral Solution (AHCHOS) placebo, while the control group receives AHCHOS and JZOL placebo. The dosage of the two drugs varies according to age and weight. The medication lasts for 7 days. The disappearance time of cough is adopted as the primary outcome. Quality control will be carried out at every stage of data management and processing to ensure that all data are reliable and processed correctly. SAS is used for statistical analysis. Intention-to-treat analysis will be carried out in this trial. All statistical tests are conducted using a two-sided test, and *p* <0.05 would be considered statistically significant.

**Discussion:** We hypothesized that children with AB could get good health benefits from JZOL. This study not only evaluates the clinical efficacy and safety of JZOL but also conducts metagenomics analysis and metabolomics analysis of feces and saliva of participants to study the mechanism of JZOL against AB. Therefore, this protocol evaluates the efficacy, safety, and mechanism of JZOL from a comprehensive perspective, so as to obtain a more solid evidence chain, which will enhance the credibility of the evidence. If successful, this study will provide a high-level evidence-based reference for the treatment of AB in children and future relevant studies.

## Introduction

Acute bronchitis (AB), also known as lobular pneumonia, is a common disease in pediatrics (Koehler, et al., 2019; Wopker, et al., 2020). The main clinical manifestations of the disease are cough, asthma, dyspnea, fever, headache, and general malaise (Kantar, et al., 2017). This disease has complex pathogenic factors and high incidence, accounting for 40% of all healthcare-associated infections in pediatric long-term care facilities (Murray, et al., 2016). Children have lower immunity than adults, so their conditions tend to change quickly. If not treated in time, it may lead to various complications, such as chronic bronchitis, emphysema, chronic obstructive pulmonary disease, *etc*., seriously affecting the quality of life of the children and their guardians (Newcombe, et al., 2010; Rolfsjord, et al., 2016). Moreover, the risk of AB is increased due to complex conditions, frequent device use, immaturity of immunity, and behavioral factors. AB spends 10 times as much in the respiratory virus season as in the non-respiratory virus season (Murray, et al., 2016). AB causes the under-five mortality rate to reach 15 percent, resulting in an estimated 808,694 child deaths (Murray, et al., 2016). Therefore, AB not only has high morbidity and mortality but also imposes a huge economic burden on society and families (Kinkade, et al., 2016; Murray, et al., 2016; Unger, et al., 2017). Currently, there is no specific treatment for AB except symptomatic supportive treatment. Antibiotics are the first choice for pure western medicine (Aabenhus, et al., 2017; Ouldali, et al., 2017). However, in recent years, the abuse of antibiotics has increased the number of drug-resistant bacteria, leading to a prolonged illness, more likely to develop into a severe illness, and then endanger life (Zanasi, et al., 2016; Bauer, et al., 2019; Walters, et al., 2022). Therefore, it is urgent to find an effective treatment for AB.

Traditional Chinese Medicine (TCM) for AB has a long history and has been widely recognized and used in Asian countries (Gottschling, et al., 2013). Jinzhen Oral Liquid (JZOL) is a TCM compound preparation, which originated from the pediatric formula “Antelope Qingfei Prescription,” with a history of more than 400 years (Tao, et al., 2020). JZOL is mainly used for acute bronchitis, mycoplasma pneumonia, viral pneumonia, and other diseases in children (Hu, et al., 2014; Yu, et al., 2019). JZOL consists of eight traditional Chinese herbs including Antelope Horn (*Saigae Tataricae Cornu*), Pingbeimu (*Fritillaria usuriensis Maxim. (Liliaceae))*, Dahuang (*Rheum officinale Baill. (Polygonaceae))*, Huangqin (*Scutellaria baicalensis Georgi (Lamiaceae))*, Niuhuang (*Bos Taurus domesticus Gmelin’s dry gallstones*), Qingmengshi (*Metamorphic biotite schist or chloritic mica carbonate schist*), Shi-gao (*Sulfate minerals gypsum family gypsum*) and Gancao (*Glycyrrhiza glabra L. (Fabaceae))* (Tao, et al., 2020). JZOL has the effect of clearing heat, detoxifying, resolving phlegm, and relieving cough (Tao, et al., 2020). Some researchers used UPLC-Q/TOF-MS technology to analyze the prototype components and metabolites in plasma, urine, bile, and feces of JZOL after intragastric administration in rats. That study described the metabolic profile of JZOL *in vivo* and preliminarily revealed its material basis *in vivo*. And the results showed that the main components absorbed into the blood by JZOL were flavonoids, saponins, and anthraquinones. The main metabolic reactions in rats were hydrolysis, hydroxylation, glycolaldehyde acidification, and sulfation (Zhang, et al., 2021). In addition, a number of clinical studies have also proved the clinical benefits of JZOL in children with refractory mycoplasma pneumoniae pneumonia (RMPP), bronchopneumonia, community-acquired pneumonia, and viral pneumonia (Hu, et al., 2019; Sun, 2020; Yang, et al., 2021; Liu, et al., 2022). In the clinical study of RMPP in children, compared with the control group, JZOL combined with methylprednisolone can effectively improve the clinical symptoms and the level of lung function, and reduce the inflammatory response, with good safety (Liu, et al., 2022). In the clinical study on the treatment of mycoplasma pneumonia in children, JZOL combined with azithromycin can reduce the levels of IL-6, IL-8, and IL-10, regulate the inflammatory response and improve the clinical symptoms with good safety (Sun, 2020).

However, the previous clinical studies lacked large sample, multi-center randomized double-blind controlled studies in terms of trial design. At the same time, in terms of intervention methods, most clinical trials adopted western medicine combined with JZOL compared with western medicine alone, which failed to fully highlight the advantages of JZOL in the treatment of AB. In terms of mechanism research, there are few laboratory studies on the mechanism of TCM treatment of AB. Therefore, a randomized, double-blind, parallel-controlled, multi-center clinical trial is designed to accurately evaluate the clinical efficacy and safety of JZOL in the treatment of AB in children. Meanwhile, this protocol will also explore the *in vivo* mechanism of JZOL in the treatment of AB through metagenomic analysis of stool or blood and metabolomics analysis of stool or blood. If completed, this study will provide high-level evidence-based support and reference for clinical treatment and drug decision-making.

## Materials and Methods

### Study Design

This clinical trial is designed as a stratified, randomized, double-blind, parallel-controlled, multi-center clinical study. The sample size is 500 participants in the intervention group and the control group respectively, with a total of 1000 participants. The trial will be carried out in 10 hospitals in China: *1*) Dongzhimen Hospital Affiliated to Beijing University of Chinese Medicine, *2*) Beijing Children’s Hospital, Capital Medical University, *3*) Children’s Hospital of Soochow University, *4*) Children’s Hospital Affiliated to Shandong University, *5*) The Second Affiliated Hospital of Heilongjiang University of TCM, *6*) Beijing Hepingli Hospital, *7*) Guangzhou Women and Children’s Medical Centar, *8*) Children’s Hospital of Shanghai, *9*) The First Affliated Hospital of Henan University of TCM, *10*) Xuzhou Children’s Hospital. All of these hospitals are qualified and experienced to conduct clinical trials. All enrolled participants will sign an informed consent before randomization. The flow chart of the trial is shown in Figure 1. There are three main objectives of the study. The first aim is to evaluate the effect of JZOL on shortening the course of AB and improving the condition in children. The disappearance time of cough is adopted as the primary outcome. The second aim is to assess the safety of JZOL in the clinical setting. The incidence of adverse events (AEs), routine blood investigations, blood biochemistry investigations, urinalysis, electrocardiogram (ECG), and stool routine tests are the main indicators to evaluate safety. The third aim is to explore the mechanism of action of JZOL in the treatment of AB by feces/saliva metagenomic analysis and feces/blood metabolomics analysis. The protocol will be reported following the Standard Protocol Items for Clinical Trials with Traditional Chinese Medicine 2018: Recommendations, Explanation and Elaboration (SPIRIT-TCM Extension 2018) (Additional file 1) (Dai, et al., 2019).

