### Sample Size Calculation

In this study, the disappearance time of cough is used as the primary outcome. According to previous studies, the disappearance time of cough in the experimental group and the control group is about 5 ± 2 days. The non-inferiority threshold of this study is set as 0.5 days, unilateral α = 0.025, power = 0.95, and the PASS (V14.0) is selected to estimate the sample size. Based on the calculation, 417 cases are needed for each group. After considering the proportion of withdrawals, the sample size of this study is 500 cases for each group, with a total of 1000 cases.

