### Intervention Method

The Intervention group takes JZOL and AHCHOS placebo, while the control group receives AHCHOS and JZOL placebo. Both drugs and their placebos are taken orally. According to different ages and weights, the dosages of the two drugs are shown in Table 1. The conditions treated by the two drugs in this study are the same as publicly available information. Ibuprofen Suspension will be taken when two groups of participants appear in an emergency. The medication lasts for 7 days. The treatment medicine and their placebos are provided by Jiangsu Kanion Pharmaceutical Co., Ltd according to the double-blind principle. The schedule of enrollment, interventions, and assessments is shown in Table 2.

**TABLE 1 T1:** Usage instructions for both drugs.

Jinzhen oral liquid and its placebo		
**Age**	**Dosage**	
2–3 years old	10 ml each time, twice a day	
4–7 years old	10 ml each time, three times a day	
8–14 years old	15 ml each time, three times a day	
Ambroxol Hydrochloride and Clenbuterol Hydrochloride Oral Solution and its placebo		
** Age**	**Weight**	**Dosage**
** 2–3 years old**	12–16 kg	7.5 ml each time, twice a day
** 4–5 years old**	16–22 kg	10 ml each time, twice a day
** 6–12 years old**	22–35 kg	15 ml each time, twice a day
** More than 12 years old**	—	20 ml each time, twice a day

Note: In case of inconsistency between age and weight, the dosage can be adjusted according to their weight.

**TABLE 2 T2:** Flow chart for clinical trial.

Stage procedure	Screening stage /Baseline (1st Visit)	During treatment (2nd Visit)<	After treatment (3rd Visit)
	−1 ∼ 0 days	5 ± 1 day	7 ± 1 day
Patient screening	×	—	—
Sign informed consent form	×	—	—
Fill in demographic information	×	—	—
Past medical history	×	—	—
Medical comorbidities and current medication	×	—	—
Chest radiograph	×	—	—
General examination	×	×	×
Physical examination	×	×	×
TCM syndrome scoring and grading	×	×	×
Routine blood investigations, urinalysis and stool examination	×	—	×
Liver function tests (ALT, ALP, AST, TBIl, γ-GT) and kidney function tests (BUN, Cr)	×	—	×
ECG	×	—	×
Stool/salivary metagenomic analysis	×	×	×
Stool/blood metabolomics analysis	×	×	×
Distribution and withdrawal of the remaining intervention medication	×	—	×
Distribution and withdrawal of patients’ medication diary record cards	×	×	×
Adverse events record	—	×	×
Combination therapy medication record	—	×	×
Conclusion (Trial Summary)	—	—	×

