### Statistical Analysis

SAS will be used for statistical analysis. Intention-to-treat analysis will be carried out in this trial, which refers to the analysis of all cases that have been randomized and used drugs at least once. All statistical tests are conducted using a two-sided test, and *p* <0.05 would be considered statistically significant. The missing data will be filled up by carrying forward the last measured value in this trial. Covariance analysis is used for the evaluation of the cough disappearance time. The group is taken as a fixed effect, and the baseline value of the cough symptom score is taken as covariance into the model for analysis. The difference between the different values of the two groups and their bilateral 95% confidence intervals are calculated. Then, the lower limit of bilateral 95% confidence intervals and the preset non-inferiority standard are compared to determine whether the test group is inferior to the control group. In addition, the subgroup analysis is performed according to age (2–3 years, 4–7 years, and 8–14 years). Measurement methods and data sets of secondary outcomes are shown in Table 5. In terms of safety, the number of AEs and SAEs during the study will be listed, and their incidence will be calculated.

**TABLE 5 T5:** Secondary outcome.

Secondary outcome	Test method	Data set
Time-lapse analysis of measured value and changed value of cough symptom score	T test is used to compare the differences between groups	FAS^a^
AUC of cough and expectoration symptom score - time		
Onset of cough relief		
Clinical recovery time		
Disappearance rate of cough, expectoration and lung rales	χ2 test or Fisher’s exact probability method is used to compare the differences between groups	
Use of antibiotics, antipyretics and analgesics		
Analysis on the curative effect of TCM syndrome	CMH chi-square is used to compare the differences between groups	

a FAS, Full Analysis Set; AUC, Area Under Curve.

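### The first aim is worded as shortening acute bronchitis, but the primary outcome has only a 0.5-day non-inferiority rule and no prespecified test of shortening

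*Protocol article*

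**What the plan says.** - **Aim.** Study Design gives the first of three aims as "The first aim is to evaluate the effect of JZOL on shortening the course of AB and improving the condition in children". The outcome attached to it follows at once: "The disappearance time of cough is adopted as the primary outcome".
- **Comparison.** Intervention Method describes a double-dummy comparison with an active drug: "The Intervention group takes JZOL and AHCHOS placebo, while the control group receives AHCHOS and JZOL placebo". There is no placebo-only arm.
- **Sizing.** Sample Size Calculation assumes that "the disappearance time of cough in the experimental group and the control group is about 5 ± 2 days", and continues: "The non-inferiority threshold of this study is set as 0.5 days, unilateral α = 0.025, power = 0.95". This leads to 417 per group, raised to 500 for withdrawals.
- **Decision rule.** Statistical Analysis fits an analysis of covariance with baseline cough score as covariate, computes a two-sided 95% interval for the group difference, and then "the lower limit of bilateral 95% confidence intervals and the preset non-inferiority standard are compared to determine whether the test group is inferior". No other rule is given for this outcome.
- **Secondary outcomes.** Table 5 assigns t tests of between-group difference to cough score, the cough and expectoration AUC, onset of cough relief and clinical recovery time. It assigns chi-square or exact tests to disappearance rates.
- **Where the hypothesis type is missing.** The Abstract, the aims in Study Design and the closing hypothesis of the Discussion, which speaks of health benefit from JZOL, do not mention non-inferiority.

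**The concern.** An aim about shortening calls for an inference about a reduction in time. The only primary inference planned is that JZOL is not worse than AHCHOS by half a day or more, which can hold when JZOL is no faster or somewhat slower.

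Nor does non-inferiority lead indirectly to shortening. There is no untreated arm, and the article gives neither evidence that AHCHOS shortens cough nor a basis for the 0.5-day margin. The Introduction says "Currently, there is no specific treatment for AB except symptomatic supportive treatment".

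What is at stake is the conclusion the report may draw. If non-inferiority is met, a statement that JZOL shortens the illness would either read non-inferiority as benefit or rest on a comparison with zero for which no rule was fixed in advance.

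**Working it through.** **Inputs.** From Sample Size Calculation: margin 0.5 days, one-sided alpha 0.025, power 0.95, mean 5 days in both groups (true difference 0), SD 2 days, 417 evaluable and 500 enrolled per group. Below, d is the true difference JZOL minus AHCHOS in days; negative means JZOL is faster.

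**1. Reproduce the plan's figure.** Normal approximation: n = 2 × SD² × (1.960 + 1.645)² / margin² = 2 × 4 × 12.99 / 0.25 = 415.8, so 416 per group. With the noncentral t distribution the smallest n giving 95% power is 417, the stated number. The trial is therefore sized for non-inferiority alone, at a true difference of zero.

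**2. Precision.** SE = 2 × √(2/n).
- n = 417: SE = 0.1385; half-width = 1.96 × 0.1385 = 0.271 days.
- n = 500: SE = 0.1265; half-width = 1.96 × 0.1265 = 0.248 days.

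**3. Slowest observed JZOL result that still passes.** Non-inferiority requires observed difference + half-width < 0.5.
- n = 417: 0.5 − 0.271 = 0.229 days slower.
- n = 500: 0.5 − 0.248 = 0.252 days slower.

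**4. Chance of passing when JZOL is truly slower.** P = Φ((0.5 − d)/SE − 1.96). For d = +0.2:
- n = 417: Φ(0.3/0.1385 − 1.96) = Φ(0.206) = 58%.
- n = 500: Φ(0.3/0.1265 − 1.96) = Φ(0.412) = 66%.

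For d = +0.5, P = Φ(−1.96) = 2.5% at either size.

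**5. Power of a superiority step on the same interval (upper limit below 0).** Noncentral t, SD 2, one-sided 0.025:

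| True gain with JZOL | 417 per arm | 500 per arm |
|---|---|---|
| 0 (the plan's assumption) | 2.5% | 2.5% |
| 0.2 days | 30% | 35% |
| 0.3 days | 58% | 66% |
| 0.4 days | 82% | 88% |
| 0.5 days | 95% | 98% |

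Under the plan's own assumption, at 417 per arm, non-inferiority is met 95% of the time and shortening relative to AHCHOS would be shown 2.5% of the time.

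**6. Alpha.** If the upper limit lies below 0 it also lies below +0.5. Superiority is nested within non-inferiority, so testing it second on the same 95% interval needs no adjustment.

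**The case against.** Four points weigh on the other side.

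- **Wording of the aim.** A reader might infer that the trial sets out to prove superiority over AHCHOS. The text does not say that: the verb is evaluate, and no comparator is named. This stands. The fault is a mismatch between aim and rule, not a declared superiority hypothesis left untested.
- **Secondary tests.** A reader might infer that shortening is never tested at all. Table 5 contradicts this, since clinical recovery time bears directly on the course of illness and is tested for difference. This stands too. The gap is confined to the primary outcome.
- **Size of the tolerated delay.** A reader might infer that an observed delay of half a day would pass. It would not: the confidence limit, not the point estimate, must clear 0.5 days. Equally, the Introduction's remark that no specific treatment exists makes an exception for symptomatic support, so it does not show that AHCHOS has no effect on cough.
- **A superiority step is optional.** A non-inferiority trial need not have one, and such a step may sit in an analysis plan or full protocol that is not shown. Its absence alone would be no finding. The point rests instead on what the article does state: an aim, a primary outcome and a decision rule, where the rule does not answer the aim as worded.

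**Conclusion.** The point holds in limited form. The first aim speaks of shortening the illness; the primary outcome carries only a 0.5-day non-inferiority rule, and the Abstract, aims and stated hypothesis do not say so. The non-inferiority analysis remains usable and its sample size reproduces. What needs correcting is the stated objective and the conclusion the primary result may support.

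The size: the criterion can be met with JZOL observed up to about 0.23 days (417 per arm) or 0.25 days (500 per arm) slower. This rests on the plan's SD of 2 days, a 1:1 comparison of means, and no gain in precision from the baseline covariate.

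A reader might also infer that adding a superiority step would ensure an answer on shortening. That is not supported. The plan assumes no difference, and power reaches 80% only for gains of roughly 0.35 to 0.39 days, which nothing in the article leads one to expect. The step fixes in advance how the interval will be read; it does not make a positive result likely.

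**What to change.** 1. In the Abstract and Study Design, state the primary objective as non-inferiority of JZOL to AHCHOS in cough disappearance time, margin 0.5 days.
2. In Statistical Analysis, add a fixed sequence on the same analysis of covariance and the same two-sided 95% interval, defining the difference as JZOL minus AHCHOS in days. Step one is non-inferiority: upper limit below +0.5. Step two, taken only if step one is met, is superiority: upper limit below 0. Stating the direction matters because the current text refers to the lower limit without saying which way the difference is taken; that is a separate matter, but the new wording should settle it.
3. State that a conclusion of shorter cough than AHCHOS is drawn only if step two is met, and that otherwise the conclusion is limited to non-inferiority.

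The cost is a few sentences, fixed before unblinding: no extra patients, no alpha adjustment and no new model.

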**FIGURE 1 F1:**
[figure not shown]
Flow diagram of the trial.

### Participants

#### Diagnostic Criteria

(1) Diagnostic criteria of Western medicine

AB is diagnosed if the child has respiratory symptoms such as cough, combined with lung crackles and/or chest radiographic changes (Hu, et al., 2014).

AB is diagnosed when there are primary symptoms, plus three secondary symptoms, concerning tongue and pulse condition (China Association of Chinese Medicine, 2012).

#### Inclusion Criteria

(1) Participants with AB under the diagnostic criteria of Western medicine.(2) Those who meet the TCM diagnostic criteria of phlegm-heat stasis in lungs.(3) Participants aged 2–14 years.(4) Cough (day + night) score ≥4 points.(5) Duration of disease ≤48 h, no antibiotics, antitussives, phlegm-reducing drugs, and other Chinese or Western medicine that influence cough has been used before treatment.(6) The informed consent process complies with the regulations, and the legal representative and/or the child (≥8 years old) signs the informed consent.

